### Quality control

Therapists will keep a weekly log of each session, including attendance, level of participation, activities that were preferred, not correctly understood, or not appreciated by participants. All participants will be encouraged to keep a mindfulness diary, in which information such as impressions, home practice, formal and informal meditations, time spent meditating in the past week, hospital visits, sick days, and general wellbeing could be logged in. Videotaping of each session will ensure intervention validity, as both therapists will receive 1 h of clinical supervision for each session, provided by two duly trained MBSR and mindfulness-based cognitive therapy (MBCT) psychologists from the Centre de consultation psychologique specialisé of the Université Catholique de Louvain (Belgium) who will review the videos.

### Pilot study endpoints

Based on previous research, the following criteria will be evaluated in order to assess the feasibility of a subsequent, larger trial
[57]:

1. Recruitment and retention: Recruitment effectiveness will be closely monitored and documented, along with recruitment strategies. Ineffective strategies will be eliminated in subsequent trials. Retention and attrition rates will also be taken into consideration in developing further trials, especially in regards to future estimates of sample sizes and inclusion/exclusion criteria, if relevant.

2. Feasibility and design assessment: Notes will be taken regarding design flow and overall progress of this project, namely the time frame required to complete each step planned in this design and the overall study.

3. Intervention and measure assessment: Participants will be asked to provide feedback to the therapists regarding their appreciation of the mindfulness intervention. They will also be asked if they would recommend this intervention to peers with cancer. Measure assessment and acceptability will be evaluated according to rates of completion of each questionnaire after the last assessment point. Thus, measures with low completion rates or poor understandability will be reconsidered for subsequent, larger trials.

4. Outcome assessment: Statistical analyses will provide indications of potential beneficial effects of the mindfulness intervention, namely with effect sizes as indicators of the magnitude of observed improvements on mood, sleep, and quality of life. These results could help in evaluating the relevance of including these variables in further trials.

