### Participants

Based on prior studies testing cognitive-behavioral interventions in adolescents with cancer, eligible participants are adolescents aged 11 to 18 years with a diagnosis of cancer
[23-25]. In keeping with previous research, there will be no specific selection/exclusion based on type, stage, or trajectory of cancer
[11,26-28]. The intervention will be conducted in French. Therefore, participants are required to speak and understand the language. They must be willing to participate in an 8-week mindfulness meditation program and be available to complete the measures 6 months after the intervention. They must not have a diagnosis of severe mental illness.

Based on prior mindfulness intervention studies with adolescent populations and on usual number of participants in a mindfulness-intervention training group (as indicated by Kabat-Zinn and colleagues
[29] in the MBSR program) a final sample size of 28 participants is targeted
[13,29-33]. Taking into consideration attrition rates from prior research (20-30%), an additional 12 participants will be recruited
[2,34-36]. Thus, a total of 40 participants will be recruited. Participants will be randomly assigned to the experimental or control group, and immediately given a participant ID for confidentiality and anonymization purposes. Twenty adolescents will be completing the mindfulness meditation intervention, which will be taught by two trained therapists (doctoral clinical psychology student and psychiatrist). The intervention will comprise of eight weekly sessions, lasting 90 min each.

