### Randomization

Participants will be assigned to one of two groups according to a computer-generated randomization list (computerized random numbers). As such, participants will be randomly assigned with a 1:1 allocation ratio following permuted block design procedures, using block sizes of four. No stratification criteria will be used. The allocation sequence will be generated by an independent researcher not involved in this project after baseline measures, thus ensuring that therapists and recruiters are kept blind to the allocation of each participant. The allocation sequence will be password protected and only accessible by the independent researcher. The research assistant responsible for the logistics of this project - who is not part of the treatment team - will not be kept blind for allocation and will be responsible for contacting participants randomly assigned to the experimental condition.

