Participants will be guided through a breathing meditation, with a special focus on thoughts and judgments. Mindful senses will then be explored, mainly through mindful touching and breathing. Participants will complete an inhibition activity and will be asked to reflect on our natural propensity to have spontaneous negative thoughts and judgments and discussing how we can come to inhibit such thoughts. Home practice will include meditation on thoughts and judgments.

#### Week 6

Participants will be guided through a heartfulness meditation, with a special focus on self-care and sending compassion to others. A group discussion on the topic of self-care *vs.* selfishness will take place. The concept of acceptance will also be explored. The session will end with a short sitting meditation with an emphasis on acceptance. Home practice will include heartfulness meditation and mindful activities that provide self-care.

#### Week 7

Participants will be guided through the mountain meditation. In dyads, participants will be asked to recall an autobiographical memory and identify how this memory reflects their personal values. A group discussion on personal and life values will then take place. Participants will be asked to reflect whether mindfulness can be considered as a value or a tool in living in accordance with our personal values. Home practice will include any type of meditation practiced in the previous weeks, as well as a reflecting on the importance of being mindful while acting accordingly to personal values.

#### Week 8

Participants will have the choice of the type (sitting *vs*. lying down) of meditation and special focus they want to bring to the practice. Intentions set at the first session will be redistributed to all participants. Participants will be given the opportunity to exchange about the intervention and give comments and feedback to the therapists. A giant puzzle activity will take place, in which participants will be asked to write on each piece personal benefits and/or disadvantages of the intervention and their meditation practice. The session will end with the distribution of a pebble stone to each participant as a reminder of their experience.

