## Discussion

Voluntary participation to this project constitutes a potential limitation, as it could imply that adolescents and their parents who take part are individuals who are either: (1) genuinely interested in the concept of mindfulness and in the action of meditating, thus potentially displaying a higher level of mindfulness than the general population of adolescents with cancer; or (2) potentially healthier and in better shape than those who chose not to participate, as meditation can be demanding. In both cases, these potential confounds will likely limit our ability to generalize our results primarily to adolescents with cancer showing similar motivation and level of health.

We do expect recruitment challenges, specifically in terms of presenting our research to ill adolescents and their parents, convincing them to take part in this project, and the fact that pediatric cancers are less frequent than adult cancers. However, we will maximize recruitment by using multiple recruitment strategies and different avenues to publicize this study.

The risk for attrition is an additional limitation of this project. Given the target population for the study, it is possible that attrition will be observed during the process due to diverse reasons, namely deterioration of health, initiation, or reinitiation of treatment rounds. Drop-outs could also occur due to the challenging nature of the intervention. Participants may conclude that the program is not what they expected or is simply too demanding for them. Further drop-outs may occur 6 months post-intervention, as some participants may be lost to follow-up (for example, harder to reach, no longer motivated to participate in the project). In addition, the research team is weighing out different options to minimize attrition in the wait-list control group - namely, monetary compensation and/or additional iTunes gift cards.

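### Acceptability feedback goes to the therapists who deliver the programme, and the only scheduled occasion is session 8, so this pilot criterion is prone to upward bias

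*Protocol article*

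**What the plan says.** Under Pilot study endpoints, the protocol article lists four criteria for judging whether a larger trial is feasible. The third covers the intervention and the questionnaires. For the intervention it says: "Participants will be asked to provide feedback to the therapists regarding their appreciation of the mindfulness intervention". A second item follows: "They will also be asked if they would recommend this intervention to peers with cancer". No asker, occasion or denominator is given for that second item.

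The only feedback occasion in the session plan is Week 8: "Participants will be given the opportunity to exchange about the intervention and give comments and feedback to the therapists". In the same session, a group puzzle activity has participants "write on each piece personal benefits and/or disadvantages of the intervention and their meditation practice".

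The Discussion gives several expected reasons for drop-out, one of which is the programme itself: "Participants may conclude that the program is not what they expected or is simply too demanding for them".

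On numbers, the Participants section says "a final sample size of 28 participants is targeted" and "Taking into consideration attrition rates from prior research (20-30%), an additional 12 participants will be recruited". This makes 40 in total, with 20 in the experimental group.

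**The concern.** The people who receive the appreciation feedback are the people being appraised. Participants are 11 to 18 years old, the scheduled exchange takes place in the group with both therapists, and the Quality control section has every session videotaped for the therapists' supervision. That setting encourages polite answers.

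The second problem is who is in the room. Someone who gave up because the programme was too demanding is among the likeliest to rate it unfavourably, and is not there in Week 8. The article describes no approach to such participants about acceptability.

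The stake is the feasibility reading. The Statistical power section expects small effects and warns that large group differences may not be detected, so the feasibility criteria carry much of the pilot's value. A favourable acceptability result drawn mainly from those who stayed, and given to their own therapists, would be a weak basis for deciding what to change in a larger trial.

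**Working it through.** **Inputs from the protocol article**
- Final sample 28, attrition 20-30%, total recruited 40, experimental group 20 (Participants).
- Recipients of the feedback: the therapists (Pilot study endpoints, item 3; Week 8).
- Acceptability rate or threshold: none stated.

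**The article's own figure.** Recruitment = final sample / (1 − attrition).
- At 30%: 28 / 0.70 = 40, which matches the stated total.
- At 20%: 28 / 0.80 = 35.

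The plan therefore allows for the upper end of its attrition range.

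**How many could be absent at session 8.** Apply the same range to the experimental group.
- 20 × 0.20 = 4 absent, 16 present.
- 20 × 0.30 = 6 absent, 14 present.

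These are upper bounds for the stated range. The attrition figure covers the whole study, and the Discussion places some losses at the 6-month follow-up, after session 8.

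**Effect on a favourable rate.** Let D be the number absent, p_c the favourable proportion among those present and p_d the proportion among those who left.

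Rate over all 20 = [(20 − D) × p_c + D × p_d] / 20

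Overstatement = p_c − rate over all 20 = (D / 20) × (p_c − p_d)

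The values of p_c and p_d are assumptions, because the article gives neither.

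| p_c | p_d | Rate over 20, D = 4 | Overstatement | Rate over 20, D = 6 | Overstatement |
|---|---|---|---|---|---|
| 100% | 0% | 80% | 20 points | 70% | 30 points |
| 100% | 50% | 90% | 10 points | 85% | 15 points |
| 90% | 0% | 72% | 18 points | 63% | 27 points |
| 90% | 50% | 82% | 8 points | 78% | 12 points |
| 90% | 90% | 90% | 0 points | 90% | 0 points |

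Worked example, D = 6, p_c = 90%, p_d = 0%: (14 × 0.90 + 6 × 0) / 20 = 12.6 / 20 = 63%, and 90 − 63 = 27 points.

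The range is therefore 0 to 20 points with 4 absent and 0 to 30 points with 6 absent, provided leavers are no more favourable than those who stayed. Courtesy answers would come on top of this. The documents give no basis for putting a number on them.

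**The case against.** The strongest reply has four parts.

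1. **The text does not restrict the question to completers.** Item 3 speaks of participants in general and does not refer to Week 8, and the recommendation item has no stated asker or timing. A reader might infer that leavers are certainly missed and that everyone answers face to face. The article does not say so, and how leavers are approached may sit in the full protocol. This stands: missing leavers is a risk, not a fixed rule. It does not touch the choice of the therapists as recipients of the appreciation feedback, which the article states outright.

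2. **Attrition is assessed separately.** Item 1 of the same list evaluates retention and attrition, so a glowing rating beside 30% loss would not be read alone. This stands in part. An attrition rate does not separate those who left through illness or treatment from those who found the programme unsuitable, and the Discussion expects both.

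3. **Negative views have other outlets.** Therapists log attendance and disliked activities each week, outside supervisors review the videotapes, journals may be consulted, and the Week 8 puzzle invites disadvantages. These sources do show that the assessment is not closed to criticism. But the logs are kept by the same therapists, use of the journals is optional, the puzzle reaches only those present in Week 8, and the videotapes serve supervision. None supplies the views of someone who has stopped.

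4. **The large gap is an extreme.** It needs all leavers to be unfavourable and all loss to come before session 8. The Discussion names health and treatment reasons before programme burden. This stands, and it is why the size is given as a range starting at zero.

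A reader might also infer that this endpoint decides whether a larger trial goes ahead. It does not: it is part of one of four criteria, and no go/no-go rule is stated.

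**Conclusion.** The concern holds as a risk of upward bias. The article names the treating therapists as recipients of the appreciation feedback and schedules only one feedback occasion, at the end of the programme and in the group. Courtesy bias follows from that stated arrangement. Under-representation of those who stopped because of the programme's demands is plausible, but the text does not fix it.

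The documents do not support saying that the endpoint is inflated. No acceptability rate exists to be inflated, and the selection component is zero if leavers share the views of those who stayed. The bound of 20 points (4 absent) or 30 points (6 absent) rests on four assumptions: the 20-30% attrition applies equally to the experimental group, all of it falls before session 8, only attenders are asked, and every attender but no leaver is favourable. It also counts only the 20 first allocated to the programme, not wait-list participants who take it later.

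The change is worth making because it is cheap and the means already exist.

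**What to change.** Revise item 3 of Pilot study endpoints as follows.

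- Collect appreciation and the recommendation question on a short written form that carries only the participant ID. Have it returned to the research assistant described under Randomization ("The research assistant responsible for the logistics of this project - who is not part of the treatment team"), not to the therapists.
- Send the same form, with an added question on the reason for stopping, to experimental participants who stopped attending.
- Report the result over all participants allocated to the programme, with non-responders shown, next to the attrition rate from item 1.
- Keep the session 8 exchange as qualitative material.

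The cost is a one-page form and a few mailings. Participant IDs, a research assistant outside the treatment team and mailed questionnaires at 6 months are already part of the study. The downside is a probably less favourable acceptability figure.

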## Discussion

Voluntary participation to this project constitutes a potential limitation, as it could imply that adolescents and their parents who take part are individuals who are either: (1) genuinely interested in the concept of mindfulness and in the action of meditating, thus potentially displaying a higher level of mindfulness than the general population of adolescents with cancer; or (2) potentially healthier and in better shape than those who chose not to participate, as meditation can be demanding. In both cases, these potential confounds will likely limit our ability to generalize our results primarily to adolescents with cancer showing similar motivation and level of health.

We do expect recruitment challenges, specifically in terms of presenting our research to ill adolescents and their parents, convincing them to take part in this project, and the fact that pediatric cancers are less frequent than adult cancers. However, we will maximize recruitment by using multiple recruitment strategies and different avenues to publicize this study.

The risk for attrition is an additional limitation of this project. Given the target population for the study, it is possible that attrition will be observed during the process due to diverse reasons, namely deterioration of health, initiation, or reinitiation of treatment rounds. Drop-outs could also occur due to the challenging nature of the intervention. Participants may conclude that the program is not what they expected or is simply too demanding for them. Further drop-outs may occur 6 months post-intervention, as some participants may be lost to follow-up (for example, harder to reach, no longer motivated to participate in the project). In addition, the research team is weighing out different options to minimize attrition in the wait-list control group - namely, monetary compensation and/or additional iTunes gift cards.

In spite of possible limitations, this project will be one among very few aimed at improving quality of life, sleep, and mood in adolescents living with cancer. To this day, mindfulness meditation has not been empirically tested with youth suffering from this condition. This project will help in evaluating the potential benefits of such a practice on both psychological and physical health of youth with cancer. Moreover, as psychological support programs in pediatric oncology are rare, conclusive results from this project could help in creating mindfulness-based intervention programs, in order to provide the necessary psychological help to adolescents living with cancer.

## Trial status

This is a clinical trial with ongoing patient recruitment. Recruitment for this project started in September 2012, and is expected to be completed by May 2013. This trial is recorded under the number NCT01783418.

## Abbreviations

MBCT: Mindfulness-based cognitive therapy; MBSR: Mindfulness-based stress-reduction
